**Date Range for Specimens and/or Review of Medical Records:**

Examples: *01/01/1999 through 12/31/2015*, or all records through *mm/dd/yyyy*.

Note: The Date Range must include the period for collection of baseline data, as well as follow-up data, if applicable.

The study involves data that exist at the time of IRB submission **and** data that will be generated after IRB submission. Include this activity in the Methods section.

The study will use data that have been collected under another IRB protocol. Include in the Methods section and enter the IRB number from which the research material will be obtained. *When appropriate, note when subjects have provided consent for future use of their data and/or specimens as described in this protocol*.

Enter one IRB number per line, add more lines as needed

Data  Specimens  Data & Specimens ______________________________________

Data  Specimens  Data & Specimens ______________________________________

Data  Specimens  Data & Specimens ______________________________________

| Data Analysis |
| --- |

Outcome Measures:

Outcome measures included measures of depression, perceived stress, resilience and anxiety. Treatment effectiveness will be assessed utilizing the objective ratings of the Hamilton rating scale for depression – 17 item (Hamilton 1960) and self-reported Patient Health Questionaire-9 (Kroenke and Spitzer 2002). The use of two different instruments of depression outcomes comes from a meta-analysis of psychotherapy studies that showed significant differences between clinician-rated and self-report measures of improvement following psychotherapy for depression. This suggests the possibility that different symptoms are suited for subjective or objective ratings (Cuipers 2010). Perceived stress will be measured using the Perceived Stress Scale (PSS), a 10-item self-administered scale that measures the degree to which one’s life is appraised as stressful (Cohen 1983). Anxiety will be measured using the self-reported Generalized Anxiety Questionnaire (Spitzer 2006). Resilience will be assessed by the Connor-Davidson Resilience Scale (CD-RISC) (Connor-Davidson 2003). Internal consistency will be assessed in our sample by measuring omega at baseline and follow-up periods for each group separately. Quality of Life will be measured using a 6 item linear analog self-assessment (LASA), questionnaire. Respondents rate their QOL on a 0–10 numerical analog scale for each domain i.e., mental, emotional, physical, spiritual, social and overall QOL (Singh et al 2014). To measure potential mechanisms of action of SMART therapy, we will measure mindfulness using a 10-item scale, The Mindful Attention Awareness Scale (MAAS), and we will measure self-compassion using a 12-item Self-Compassion Scale- Short form(SCS-SF).

Power Calculation:

Sample size calculation is based on effect sizes obtained from the feasibility study we completed recently. Although we found a within group standardized mean difference >1 for reduction in depressive symptoms in our pilot study, we will assume a moderate standardized mean difference of 0.7 for the RCT, , alpha level =0.05 (two-tailed), power of 80%. Based on these assumptions, we will require a sample of 40 participants in each group providing allowance for 25% drop-out rate to detect statistically significant differences in depressive symptoms between the 2 groups.

Statistical Analysis:

The SMART-D and TAU groups will be compared on baseline demographic and clinical characteristics. Primary analysis will apply Intention-to-treat analysis to compare treatment outcomes of depression, with participants analyzed based on their initial randomization, at post-SMART-D intervention, at the 3 month and 6 month time post intervention time points. Analysis of the primary outcome (depression) and secondary outcomes (perceived stress, resilience) will be carried out using linear mixed effects regression with results presented as mean differences (and 95% CIs). Secondary analysis will examine the relationship of stress as a predictor of depression and depression as a predictor of stress. For each outcome, a single mixed effects model will be fitted incorporating baseline, post-intervention, 3- and 6-month data using random effects to allow for the repeated measures within an individual, and clustering of individuals within each treatment site. Separate parameters will be estimated for group differences at 3- and 6-months post-intervention; scores at baseline will be added as a covariate. Differences in the outcomes of SMART-D and TAU groups will be assessed using linear mixed models, with individuals clustered within each treatment site and assessment times clustered within individuals. We will run an unadjusted model and compare this to an adjusted model, with the unadjusted model as our primary analysis, to evaluate robustness of these findings. The adjusted model will include the following as covariates: gender, age, education, marital status, medication use (obtained from interview and chart records), number of previous depressive episodes, baseline anxiety (measured by GAD) and severity of recent depressive episode. The participant’s site and individual participant will be modelled as random effects and the remaining variables will be handled as fixed effects. Conditional maximum likelihood will be used to fit the mixed model to account for the missing data. This approach makes an assumption that data are missing at random. Sensitivity analysis in the form of pattern mixture models will be used to explore the departure from this assumption. We will also perform a per-protocol analysis as a supplementary analysis. Significance will be tested at p < .05 for the primary analysis. False Discovery Rate method will be used to make adjustments for Type I error inflation for secondary outcomes.

References

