In a recent open label feasibility study, patients with major depression were invited to participate in an adjunctive 8-week group therapy of SMART. The primary outcome measure was baseline to endpoint change in resilience as measured by the Connor Davidson Resilience Scale (CD-RISC). Secondary outcome measures included baseline to endpoint change in the Cohen’s Perceived Stress Scale, and depression [Hamilton Rating Scale for Depression (HAM-D) and Patient Health Questionnaire (PHQ-9)]. 23 participants enrolled in the study (mean age = 46±13 years, female =91%). Baseline ratings of mood were of mild to moderate symptom severity (mean HAM-D=14.5 and PHQ-9=12). 74% of participants were study completers (attended ≥ 6 sessions). In an intention-to-treat analysis, at study endpoint, there was a significant improvement in resilience (p = .03), reduction in perceived stress (p =.002) and improvement in depression (HAM-D and PHQ-9- both p<0.001). The study showed that a resilience training program focusing on wellness is feasible for patients who are currently symptomatic with major depression. It was concluded that a larger randomized controlled trial is needed to establish efficacy of this intervention and explore the long-term impact of stress management and resilience training in major depressive disorder (manuscript under review).

During the feasibility study, it was also observed that participants had difficulties in practicing self-kindness and self-compassion. These appeared to be influenced by negative self-esteem and feelings of guilt. Participants also found the topics of acceptance and forgiveness challenging. These challenges may be unique to patients with major depression with their negative cognitive biases. While the emphasis of the course was to develop resilience building strategies towards the present and future, participants showed a tendency to focus on the past and engage in rumination. As a result, modifications to the SMART program were made to create the SMART for depression (SMART-D) for the proposed study. These include specific focus on self-compassion, self-acceptance, self-forgiveness and anger as part of the coursework of modified SMART-D.

| **Study Design and Methods** |
| --- |

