Treatment as usual will consist of any ongoing medication or psychotherapy based treatments that are currently in place. Participants will be required to be under the supervision of a primary care provider or Psychiatrist or Psychologist for their major depression during their participation in the study.

| **Subject Information** |
| --- |

Target accrual: 80 subjects

Subject population (children, adults, groups): Adults from age 25 - 80

Inclusion Criteria:

- Participants will be enrolled for this study from patients attending the Mayo Clinic Depression Center, Mayo Clinic Family Medicine clinics at Rochester and Kasson, MN, Behavioral Health and Primary Care Clinic at Mayo Clinic Health System, Austin and Albert Lea, MN, and MCHS Red Wing, MN with a diagnosis of major depression with a current moderate episode, with PHQ-9 scores 10-19.
- Participants will be required to be between 25 and 80 years old
- Able to speak English
- Able to provide written informed consent to participate in the study
- Participants must have DSM-V diagnostic confirmation of major depressive disorder (MDD) (American Psychiatric Association 2013).
- Participants will continue taking any prescribed medications from their clinical treatment team.
- Participants with co-morbid secondary diagnoses of persistent depressive disorder and generalized anxiety disorders will be included in the study.
- Participants must consent to audio recording of random group sessions which will be disclosed at the final study session.
- Participants are willing to use the Mayo Clinic Patient Portal for communication purposes during the study.

Exclusion Criteria:

- Participants with bipolar disorder, active psychosis, active suicidal ideations, and active substance abuse meeting criteria for substance use disorders except nicotine, obsessive compulsive disorder, active panic disorder with agoraphobia or other phobic disorder, active posttraumatic stress disorder, active severe personality disorders will be excluded.
- Participants with a severe major depressive episode- HAM-D scores >23.
- Pregnant women – because of time duration of the study.

| **Biospecimens** |
| --- |

Collection of blood samples. When multiple groups are involved copy and paste the appropriate section below for example repeat section b when drawing blood from children and adults with cancer.

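### Forty per group less the planned 25% drop-out leaves 30 evaluable per group and about 76% power at a standardized mean difference of 0.7, not the stated 80%

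*Protocol*

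**What the plan says.** Under Data Analysis, the Power Calculation starts from the feasibility study's within-group effect, which exceeded 1, and marks it down: "we will assume a moderate standardized mean difference of 0.7 for the RCT". It sets "alpha level =0.05 (two-tailed), power of 80" per cent and concludes that "we will require a sample of 40 participants in each group providing allowance for 25% drop-out rate". Subject Information agrees on the total: "Target accrual: 80 subjects".

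The paragraph does not give the number of evaluable participants per group, the formula that turned it into 40, or a correlation between baseline and follow-up scores.

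The next section, Statistical Analysis, plans linear mixed models on all time points and says that "scores at baseline will be added as a covariate". It also names an unadjusted model as primary and an adjusted model, with a longer covariate list, as a check on robustness.

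**The concern.** A sample size that includes a drop-out allowance should still deliver the target power once the allowed drop-out has occurred. Here it does not. With the stated loss, the number remaining is below what the stated effect, alpha and power require, whether the t test or the normal approximation is used.

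The power statement is the protocol's quantitative justification for recruiting 80 people, and readers will use it to judge a null result. If it says 80% when its own inputs give about 76%, that judgement rests on a figure that is slightly too favourable.

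**Working it through.** **Inputs.** All are from the Power Calculation: SMD d = 0.7, two-sided alpha 0.05, power 80%, 40 randomised per group, drop-out 25%.

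**Step 1: evaluable participants required per group.**
- Normal approximation: n = 2 × ((1.960 + 0.842) / 0.7)² = 32.04, or 33 rounded up.
- Two-sample t test (noncentral t): n = 33.02, or 34 rounded up.

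**Step 2: trying to reproduce the stated 40.** If a fraction 0.25 is lost, the number to randomise is n / (1 − 0.25).
- 32.04 / 0.75 = 42.7, so 43
- 33 / 0.75 = 44
- 33.02 / 0.75 = 44.03, so 45 if rounded up
- 34 / 0.75 = 45.3, so 46

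The range is 43 to 46 per group (86 to 92 in total), and none of these gives 40. One-sided alpha does not give it either: 26 / 0.75 = 34.7, so 35.

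Multiplying does reach the figure: 32 × 1.25 = 40. Since 32 / 0.80 is also 40, the stated number matches a 20% loss. A baseline-adjusted calculation with an assumed correlation of 0.3 comes close too: 33.02 × (1 − 0.3²) / 0.75 = 40.07. The protocol shows neither step, so its arithmetic cannot be identified.

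**Step 3: power delivered.** Evaluable per group = 40 × 0.75 = 30. By the normal approximation, power is Φ(0.7 × √(30/2) − 1.960) = Φ(0.751).

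| Evaluable per group | Power, t test | Power, normal |
|---|---|---|
| 30 | 76.0% | 77.4% |
| 32 | 78.7% | 80.0% |
| 33 | 80.0% | 81.2% |
| 34 | 81.2% | 82.3% |

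**Step 4: detectable effect with 30 per group at 80% power.** By the t test it is 0.736. By the normal approximation it is (1.960 + 0.842) × √(2/30) = 0.723.

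**Step 5: drop-out that 40 per group can absorb at 80% power.**
- 1 − 34/40 = 15.0%
- 1 − 33.02/40 = 17.4%
- 1 − 32.04/40 = 19.9%

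**Step 6: what baseline adjustment could recover.** Take d = 0.7 on the raw-score scale. Adjusting for a baseline score with correlation ρ multiplies the residual variance by 1 − ρ². For 30 per group to reach 80%, 1 − ρ² must be at most (0.70 / 0.7356)² = 0.9055, so ρ must be at least 0.307. The t-test approximation gives 77.7% at ρ = 0.2, 79.8% at 0.3 and 82.9% at 0.4. These correlations are assumptions; the protocol gives none.

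**The case against.** The best counter-argument is that a t test on 30 completers per group is not the planned analysis. The protocol plans an intention-to-treat mixed model with the baseline score as a covariate, and people who leave after the post-intervention assessment still contribute data. A moderate baseline correlation would restore 80%. This stands as a comment on the design, and it is why one should not infer that the trial as a whole is underpowered. It does not rescue the sentence in the Power Calculation, which assumes no correlation and claims no gain from repeated measures. Calling the unadjusted model primary also leaves some doubt about how far baseline adjustment belongs to the primary analysis.

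A second objection is that the gap is small, that 0.7 is itself a judgement, and that results will be reported with confidence intervals. That is right, and it limits the weight of the point.

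Three stronger readings are tempting, but the documents do not support them:
- **That drop-out was added by multiplying by 1.25.** The number is consistent with this, but the step is not shown and other routes land at or near 40. The shortfall does not depend on the cause.
- **That the pilot shows 25% to be too low an allowance.** The feasibility study reports that "74% of participants were study completers (attended ≥ 6 sessions". That is session attendance, not missing outcome data, and no rate of missing outcomes is given. This trial counts 3 of 6 contacts as completion, allows remote assessment and pays for each assessment.
- **That clustering within therapy groups pushes power lower by a known amount.** SMART-D is delivered in groups of 4 to 8, so some loss is possible, but the protocol gives no intraclass correlation. Any figure would rest on an outside assumption, and the question is separate from this arithmetic.

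**Conclusion.** The point holds as a modest arithmetic correction. On the protocol's own inputs, 40 per group with 25% drop-out gives 76.0% power (t test) or 77.4% (normal approximation). That is 2.6 to 4.0 points below the stated 80%, or 3 to 6 randomised participants per group too few for that claim.

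The result assumes a simple comparison of two equal groups at one time point, with drop-outs contributing nothing. That is the only calculation the stated inputs support. A reader might infer that a null result would be uninterpretable; a gap of this size does not support that.

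**What to change.** Keep the total at 80 and reword the power paragraph in one of two ways.

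1. State that 40 randomised per group, 30 evaluable after 25% drop-out, give about 76% power at SMD 0.7 (80% at an SMD of about 0.74) for a simple two-group comparison, two-sided alpha 0.05.
2. If the sponsor relies on the baseline-adjusted mixed model, say so, state the assumed baseline/follow-up correlation with its justification, and confirm that the primary model includes the baseline score. About 0.31 or more restores 80%, before any allowance for therapy-group clustering.

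In either case, show the evaluable number and the inflation formula. The cost is one paragraph and, under the first option, a slightly less favourable power figure. No extra participants, visits or procedures are needed. Keeping 80% for the simple comparison at SMD 0.7 would instead take about 43 to 46 per group, which is 6 to 12 more participants in total; correcting the statement does not require this.

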The SMART-D intervention group will comprise of between minimum 4 to maximum 8 research participants per group. The SMART-D intervention will be primarily delivered by 2 therapists with one lead therapist (study PI, [name]) and one co-therapist (Co-I, [name] or [name]) for all groups. The sessions will be provided utilizing a HIPPA compliant real-time audio visual connection via Zoom video through the Patient Portal or telephone calls with the first 4 of 6 sessions occurring weekly and sessions 5 and 6 occurring on week 6 and week 8. In the event of emergencies where the therapist is not available, provisions will be made to have the session delivered by a second therapist, who is also proficient to deliver the intervention (study Co-Investigators – [name] or [name]). Each session will be 75-90 minute duration, occurring weekly at the same time of the week, except on holidays or inclement weather. The sessions will include a brief introduction and review of homework assignments, followed by a presentation, based on the book “*Mayo Clinic Guide to Stress Free Living*”, and a group discussion of each topic presented. The content of the sessions have been modified in collaboration with the creator of the program based on findings from the feasibility study conducted earlier (see Table 2). To ensure fidelity of the intervention, the study team will select, at random, 1-2 sessions per group to be audio recorded and reviewed by content experts within the research team. SMART-D participants who complete 3 out of 6 contact points will be considered study completers.

Table 2: Structure of Sessions SMART-D

| **Agenda** | **Insight** | **Practices** | |
| --- | --- | --- | --- |
|  |  | Core | Supplementary |
| Week 1 | Science of Stress, The SMART Approach, Gratitude | Morning gratitude | Grateful note, Gratitude jar |
| Week 2 | Mindful Presence and Kindness | Two-minute rule:  Kind Attention | Curious Moments, Kindness to Self,  10 minute relaxation |
| Week 3 | Resilient Mindset- I | Gratitude, Compassion | Dropping one, Finding Inspiration |
| Week 4 | Resilient Mindset-II | Meaning, Acceptance, Forgiveness | Resilient living (Pick One habit) |
| Week 6 | SMART- Integrated approach-I | Integrate core practices | Develop individual ideas |
| Week 8 | SMART- Integrated approach-II |  | Develop individual ideas |

Treatment as Usual:

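### The primary mixed model has no term for the SMART-D therapy group, so if outcomes correlate within groups the between-arm standard error is understated and type I error exceeds 5%

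*Protocol*

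**What the plan says.** **Delivery.** The Intervention section states: "The SMART-D intervention group will comprise of between minimum 4 to maximum 8 research participants per group". Sessions include "a group discussion of each topic presented" and run by Zoom or telephone. One lead therapist, with a co-therapist, takes all groups.

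**Comparator.** Under Treatment as Usual, participants continue whatever medication or psychotherapy they already have. The trial forms no groups in this arm.

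**Model.** The Statistical Analysis section specifies linear mixed models "with individuals clustered within each treatment site and assessment times clustered within individuals". It then settles the random part: the participant's site and "individual participant will be modelled as random effects and the remaining variables will be handled as fixed effects". Therapy group appears in neither the unadjusted (primary) nor the adjusted model.

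**Sample size.** The Power Calculation section says "we will assume a moderate standardized mean difference of 0.7 for the RCT", with "alpha level =0.05 (two-tailed), power of 80"%, and concludes that "we will require a sample of 40 participants in each group providing allowance for 25% drop-out rate". It mentions no ICC or design effect.

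**The concern.** The design is partially nested. SMART-D participants share sessions and discussion with the same few people, while TAU participants do not. Outcomes within a therapy group may therefore be correlated, and that correlation arises in one arm only.

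The two random effects in the plan do different jobs. The participant effect handles repeated measurements on one person. The site effect is common to both arms, so it largely cancels from the arm contrast. A group effect confined to SMART-D does not cancel.

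At stake are the primary test at p < .05 and the 95% confidence intervals for the mean differences. For any positive ICC the error runs one way: intervals too narrow and p-values too small.

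This is not a detail left open for a statistical analysis plan. The protocol lists the random effects and declares everything else fixed, so an analysis that follows it leaves the group level out.

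**Working it through.** **Inputs from the protocol.** Standardised mean difference 0.7, two-sided alpha 0.05, power 80%, 40 per arm, 25% dropout (Power Calculation); group size m = 4 to 8 in SMART-D only (Intervention). Forty participants give 40/8 = 5 to 40/4 = 10 groups.

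**Assumed input.** The therapy-group ICC, which the protocol does not give: 0.01, 0.05 and 0.10.

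**Step 1: reproduce the stated sample size.** n per arm = 2 × (1.960 + 0.842)² / 0.7² = 32.04, and 32.04 × 1.25 = 40.05. The stated 40 per arm is reproduced under independent observations, so it contains no allowance for therapy groups.

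**Step 2: variance of the arm difference.** With equal arms and clustering in SMART-D only, the design effect in that arm is DE = 1 + (m − 1) × ICC. True variance divided by model variance is R = (DE + 1)/2.

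**Step 3: actual type I error** = 2 × [1 − Φ(1.96/√R)]. The rows for m = 3 and m = 6 bracket the case in which 25% dropout is spread evenly (4 × 0.75 = 3; 8 × 0.75 = 6).

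| ICC | m | DE | R | Type I error |
|---|---|---|---|---|
| 0.01 | 4 | 1.03 | 1.015 | 5.2% |
| 0.01 | 8 | 1.07 | 1.035 | 5.4% |
| 0.05 | 3 | 1.10 | 1.050 | 5.6% |
| 0.05 | 4 | 1.15 | 1.075 | 5.9% |
| 0.05 | 6 | 1.25 | 1.125 | 6.5% |
| 0.05 | 8 | 1.35 | 1.175 | 7.1% |
| 0.10 | 3 | 1.20 | 1.100 | 6.2% |
| 0.10 | 4 | 1.30 | 1.150 | 6.8% |
| 0.10 | 6 | 1.50 | 1.250 | 8.0% |
| 0.10 | 8 | 1.70 | 1.350 | 9.2% |

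**Step 4: does the site effect absorb the correlation?** Null trials were simulated with 40 per arm, 5 sites, one follow-up time, a baseline covariate, a random site effect and no group term. There were 4,000 trials per setting, with a Monte Carlo error of about 0.3 to 0.5 points.

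| ICC | m | Groups across sites | Groups within sites |
|---|---|---|---|
| 0 | 8 | 5.6% | 4.8% |
| 0.05 | 4 | 5.0% | 6.4% |
| 0.05 | 8 | 7.6% | 6.8% |
| 0.10 | 4 | 6.9% | 7.1% |
| 0.10 | 8 | 9.9% | 10.5% |

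With small groups and ICC 0.05 the excess is within or close to simulation noise. With groups of 8 it is clear however groups relate to sites. The site effect does not remove it.

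**Step 5: power once the clustering is counted.** Power = Φ(0.7/√(2R/30) − 1.96), with 30 completers per arm (40 × 0.75).
- ICC 0: 77%.
- ICC 0.05: 74% (m = 4) to 71% (m = 8).
- ICC 0.10: 72% to 65%.
- With the smaller post-dropout groups (m = 3 to 6): 75% to 72% at ICC 0.05, and 73% to 68% at ICC 0.10.

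**The case against.** The strongest objection is that nothing in the protocol shows the ICC to be above zero. Content is standardised (Table 2, based on one book) and fidelity is checked by reviewing recordings, which may keep differences between groups small. At ICC 0.01 the effect is negligible. Dropout shrinks the groups that contribute data, and correlation may fade by 3 and 6 months, after sessions have ended. All of this stands. It limits what can be said about size, but it does not supply the missing term.

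Several stronger readings are tempting and not supported:

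- **That type I error is certainly, or greatly, above 5%.** This would need a known ICC. The largest figures require ICC 0.10 together with full groups of 8.
- **That sharing therapists drives the correlation.** One lead therapist takes all groups, and a person common to every group cannot make groups differ from one another. The argument here rests on shared sessions and discussion.
- **That groups are closed.** The Intervention section gives group size and schedule but does not say so. The point does not need it.
- **That Zoom delivery ("The sessions will be provided utilizing a HIPPA compliant real-time audio visual connection via Zoom video") proves groups cut across sites.** The protocol does not say how groups are formed in relation to sites. The simulation shows inflation with groups of 8 either way.
- **That site should become a fixed effect.** That is a separate modelling preference and does not follow from therapy-group clustering.

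A TAU participant could also be in some group psychotherapy as part of usual care. The protocol does not describe this as a design feature, and it would not justify omitting the groups the trial itself creates.

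**Conclusion.** The omission is certain: the primary model names site and participant as its random effects and leaves out the level that the intervention creates. The consequence is conditional on outcomes correlating within therapy groups. If they do, the standard error of the arm difference is too small and the nominal 5% is exceeded, from barely at ICC 0.01 to 6.8%-9.2% at ICC 0.10 with full groups, and less after the planned dropout.

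These figures assume equal arms, a single time point, equal group sizes and the stated ICCs, none of which comes from trial data. Because the size is unknown, this is a should-fix matter: the term belongs in the primary model, but the documents do not show that the planned test is badly invalid.

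**What to change.** - Add to the primary model a random therapy-group effect that applies to the SMART-D arm only (a partially nested model, with each TAU participant treated as ungrouped). Use Satterthwaite or Kenward-Roger degrees of freedom. Specify this before the data are analysed.
- Carry the therapy-group ID in the analysis dataset. The protocol does not say that it goes unrecorded, but the analysis cannot be done without it.
- State the assumed ICC and the resulting power in the Power Calculation section.

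**Cost.** The change is one model term and one variable, but it is not free. Intervals widen. With only 5 to 10 groups the group variance is poorly estimated. In a balanced single-time-point simulation (40,000 null trials per setting) it came out as zero in about 40% of trials at ICC 0.05. The Satterthwaite test was slightly conservative, rejecting in roughly 3.5% to 4.8% of null trials across ICC 0 to 0.10. Realised power with 30 completers per arm falls from about 77% to 71%-74% at ICC 0.05, so the sponsor should either accept that power openly or revisit the sample size.
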